**Fig. 3 Fig3:**
[figure not shown]
Lower body positive pressure (Alter G)

##### Sample size calculation

G Power software analysis version 3.1.9.2 (University of Kiel, Kiel, Germany) was used to determine the sample size using pain level changes following intervention from a prior study [12]. With a small effect size of 0.29, *α* level of 0.05, and power of 0.80, the required sample size is 22 participants (11 participants per group). With a 20% attrition rate, there will be a total of 26 participants for total sample (13 participants in each group).

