**Methods:**

The study is a single blind randomized clinical trial with two independent groups. This study will enroll 26 participants with mild to moderate knee osteoarthritis. The participants will be randomized into either experimental group (backward walking exercise) or control group (forward walking exercise). Both groups will use lower body positive pressure treadmill for walking exercise. Both groups will perform regular conventional exercise and worm-up exercise before walking exercise. The treatment will be three times a week for six weeks. Walking session will be up to 30 min each session. Data collection will be collected during pre- and post- intervention including primary outcomes including numeric pain rating scale (NPRS), knee injury and osteoarthritis outcome score (KOOS), and thigh muscle strength test. The secondary outcomes include five times sit to stand test (FTSTS), 3-meter backward walk test (3MBWT), timed up and go test (TUG), four square step test (FSST), functional reach test (FRT), 10-meter walk test (10-MWT), six minute walk test (6MWT), medical outcomes study short form 12 (SF-12), patient health questionnaire -9 (PHQ-9), and rapid assessment of physical activity (RAPA). An independent t-test will be used to evaluate the effect of treatment on the outcome measures.

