## Introduction

Osteoarthritis (OA) is a joint degenerative disease affecting more often adults aged 65 year and older [1]. Globally, the pooled prevalence on knee OA was 16% in people aged 15 and older and 22.9% in those aged 40 and older [2]. Knee OA is the most common arthritis [3] that causes disability and interferes with activities of daily life (ADLs) [4], and quality of life [5], and increases the risk of fall [6]. Several symptoms are associated with knee OA including pain, stiffness, knee muscle weakness, compromised joint integrity, poor balance, and limited knee range of motion [7, 8]. However, non-surgical interventions such as physical therapy, exercise, and manual therapy along with patient education are important and often efficacious for improving patient-related outcomes in individuals with knee OA [9, 10].

Walking exercise is an effective and recommended treatment for individuals with knee OA in minimizing pain and disability [11]. Likewise, backward walking exercise was efficacious in reducing knee OA symptoms than forward walking exercise [12]. Backward running also reduces compressive stresses at the patella-femoral joint, compared with forward running [13], which may alleviate knee pain and improve knee function. Backward walking training have been reported to increase quadriceps muscle strength in individuals with knee OA [12, 14].

Adding backward walking exercise to a traditional treatment program for three weeks improved function and decreased disability in individuals with knee OA [15]. Furthermore, six weeks of backward walking exercise resulted in a higher decline in pain and functional disability compared to forward walking exercise and control groups which receive conventional physical therapy, as well as improved quadriceps muscle strength and performance [12]. However, there was no significant difference between forward walking and backward walking exercise in all outcome measures. Furthermore, forward walking exercise and backward walking exercise were on overground which may increase the force on the knee due to the body weight loading and limit the exercise duration which was 10 min.

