##### Numeric pain rating scale (NPRS)

The 11-point NPRS measures pain severity from 0 to 10, where 0 indicates "no pain" and 10 indicates "worst imaginable pain." The NPRS has excellent internal consistency (Coefficient alpha = 0.84) [19] and has been validated to evaluate pain severity [20]. Minimal clinically important difference (MCID) in individuals with osteoarthritis is from 1 to 1.7 points or a change of 15–27.9% [21, 22]. At baseline, participants will rate their pain over the past 24 h using the NPRS. The NPRS will be taken before each session, throughout gait training, and after six weeks.

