### Statistical analysis

The collected data will be analyzed with IBM SPSS version 28.0 (IBM Corp., Armonk, NY, USA). The descriptive demographic data (means, medians, standard deviation, and frequencies) include age, gender, onset of knee OA, height, weight, knee involved, and all primary and secondary outcome measures will be computed and compared between two groups at the baseline using independent t-test. The Shapiro–Wilk test will be used to evaluate the normality assumption. A dependent *t*-test or Wilcoxon signed rank test will be performed to evaluates the difference between pre-intervention and post-intervention. The independent *t*-test or Mann–Whitney *U*-test will be performed to evaluate the difference between groups at the baseline and post-intervention. The level of significance will be set at *p* < 0.05.

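### An effect size of 0.29, described as small, does not give 22 participants at 80% power for the planned independent t-test, and the metric and test behind the calculation are not named

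*Protocol article*

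**What the plan says.** The Sample size calculation section of the protocol article says that G*Power was used with pain changes from a prior study. It gives the first input as "With a small effect size of 0.29", sets alpha at 0.05, and continues "and power of 0.80, the required sample size is 22 participants (11 participants per group"). It then allows for 20% attrition and arrives at 26 in total, 13 per group. It does not name the effect-size metric, the test family, the sidedness, the number of measurements or any correlation between measurements.

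The analysis is stated in two places. The abstract says: "An independent t-test will be used to evaluate the effect of treatment on the outcome measures". The Statistical analysis section says that an independent t-test or Mann–Whitney U-test "will be performed to evaluate the difference between groups at the baseline and post-intervention". Within-group change is tested separately by a paired t-test or Wilcoxon test. The Study design section sets two assessment times, baseline (T0) and after six weeks (T1). No repeated-measures ANOVA or ANCOVA appears.

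**The concern.** For a two-group t-test, alpha, power and the standardised difference fix the sample size. A small standardised difference needs well over a hundred participants per arm, so 11 per arm is out of line on sight.

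The power statement is the only quantitative justification for the size of the trial. If it does not hold for the test that will be run, the stated chance of detecting the effect that the trial was sized for is wrong, possibly by a wide margin. A non-significant comparison would then carry far less information than 80% power suggests.

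**Working it through.** **Inputs.** Effect size 0.29, alpha 0.05, power 0.80, 11 per group required, 20% attrition and 13 per group enrolled (all from Sample size calculation); 1:1 allocation (Allocation sequence generation); independent t-test (abstract and Statistical analysis). Two-sided testing is assumed because sidedness is not stated.

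**1. Planned test, 0.29 read as d.** The normal approximation is n per group = 2(z₀.₉₇₅ + z₀.₈₀)²/d² = 2(1.960 + 0.842)²/0.29² = 186.7, so 187. The exact non-central t gives 188 (power 0.8008; 187 gives 0.7987), or 376 in total. One-sided testing still needs 148 per group.

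With 11 per group, the non-centrality is d√(n/2) = 0.29 × √5.5 = 0.68, against a critical t of 2.086 on 20 degrees of freedom. Power is 9.9% (16.2% one-sided). With 13 per group it is 10.9%.

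**2. Other readings of 0.29, same t-test.**

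| Reading | Equivalent d | n per group for 80% | Power at 11 per group |
|---|---|---|---|
| Cohen's d | 0.29 | 188 | 9.9% |
| Cohen's f, d = 2f | 0.58 | 48 | 25% |
| Correlation r, d = 2r/√(1−r²) | 0.61 | 44 | 27% |
| f², d = 2√0.29 | 1.08 | 15 | 67% |
| Eta-squared, d = 2√(0.29/0.71) | 1.28 | 11 | 81% |

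On the conventional benchmarks, 0.29 lies between small (0.2) and medium (0.5) as d, just below medium (0.3) as r, and above medium (0.25) as f. As f² or eta-squared it corresponds to a d above 1.

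**3. Reproducing the plan's 22.** Two kinds of calculation return it:
- Eta-squared = 0.29 with the planned t-test, as in the last row of the table.
- A repeated-measures ANOVA (within-subject or interaction effect) with f = 0.29 and two groups, using λ = f²·N·m/(1−ρ) for m measurements with correlation ρ. With m = 3 and ρ = 0.5, λ = 0.0841 × 22 × 3/0.5 = 11.10 on 2 and 40 degrees of freedom, power 82.7%. With m = 2 and ρ = 0.6, λ = 0.0841 × 22 × 2/0.4 = 9.25 on 1 and 20 degrees of freedom, power 82.5%. With m = 2 and ρ = 0.5, N = 22 gives only 73.5% and 26 are needed before attrition.

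**4. What the planned test can detect.** The standardised difference with 80% power, two-sided 0.05, is 1.15 with 13 per group, 1.26 with 11 and 1.32 with 10.

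**5. Attrition.** To keep 22 after 20% loss requires 22/(1−0.20) = 27.5, so 28 (14 per group). The figure 26 matches 22 × 1.2 = 26.4 rounded down. Losing 20% of 13 leaves 13 × 0.8 = 10.4, so about 10 evaluable per group.

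**The case against.** The best defence is that the metric is unnamed, so 188 per group and 10% power are conditional on d. This stands. The eta-squared reading matches the planned test, alpha, power and 22 participants; what it contradicts is the description of the effect as small. It is therefore too strong to say that 80% power is impossible on every reading, that only a repeated-measures ANOVA yields 22, or that d is the only scale on which 0.29 is small: it is also below medium as r.

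A second defence is that a repeated-measures model was intended. Pain is in fact recorded more often than T0 and T1, since the NPRS section has it taken before each session and during gait training. But the Statistical analysis section plans no model that uses those readings, so a calculation built on one does not describe the planned comparison.

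Three further inferences are tempting but not supported:
- The Introduction says of the earlier trial: "However, there was no significant difference between forward walking and backward walking exercise in all outcome measures". A reader might conclude that it cannot supply an effect size for this contrast. However, a non-significant contrast still has a point estimate, the preceding sentence reports a greater fall in pain with backward walking, and the source itself is not available to show which contrast gave 0.29.
- The NPRS section says that the minimal clinically important difference "in individuals with osteoarthritis is from 1 to 1.7 points". A reader might conclude that the trial cannot detect it. The document gives no standard deviation, and it also expresses that threshold as a percentage change, so setting it against a between-group difference needs assumptions that the text does not provide.
- Nothing in the protocol says that a non-significant result will be reported as no difference. The safeguard proposed below is a precaution and does not correct a stated intention.

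**Conclusion.** The point holds in conditional form. The stated effect size, its description as small, the planned t-test, 80% power and 22 participants cannot all be true together.

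If 0.29 is d, the required number is about 17 times the stated one (188/11) and power is about 10%. If it is f or r, the required number is about four times as large (48 or 44 against 11) and power is 25% to 27%. The one reading of those checked that restores 80% for the planned test makes the effect large; the others that return 22 rely on an analysis that is not planned. These figures assume two-sided testing and a t-test on the full evaluable sample. A Mann–Whitney test would need somewhat more under normality (about 197 per group for d = 0.29).

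The attrition error is separate and minor beside this: 28 rather than 26 would be needed to keep 22.

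**What to change.** Keep the 26 participants and rewrite the sample size paragraph:

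- Name the effect-size metric, the G*Power test, the sidedness and any number of measurements and correlation entered.
- Replace the power claim with one for the planned test: at two-sided 0.05, 80% power only for a standardised between-group difference of about 1.15 with 13 per group, 1.26 with 11, or 1.32 with 10, the last being about what 20% attrition leaves.
- If 0.29 proves to be d, state that power for it is about 10%. If it is another metric, give the corresponding figure instead.
- Correct the attrition sentence: either say that 26 enrolled leaves about 10 per group after 20% loss, or that keeping 22 would need 28.
- State that the result will be the between-group NPRS difference with a 95% CI, and that a non-significant test will not be taken as evidence of no difference.

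The cost is rewording and a less favourable stated power. No extra participants are needed unless the sponsor wishes to keep a claim of 80% power for a small effect, in which case the number must be recalculated for the planned test.

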### Participants and recruitment

A sample consisting of 26 men and women with knee OA is required to be allocated to each group (*n* = 13 per group). The participants will be recruited from surrounding communities. All participants will read and sign an informed consent form that describes the study protocol, risks, and benefits. Figure 2 depicts the study’s expected timeline for enrollment, evaluation, and treatment. All data collection and intervention will take place at the Qassim University Medical City's physical therapy department in Saudi Arabia.

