### Procedure

#### Assignment of intervention

##### Allocation sequence generation

In a ratio of 1:1, the participants will be allocated randomly into an experimental group (EG, *n* = 13) or a control group (CG, *n* = 13), using an online randomization website (https://www.graphpad.com/quickcalcs/randomize1.cfm), a research assistant who is not involved in the intervention or data collection will generate the randomization.

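### Enrolling 26 does not cover 20% attrition: 20 or 21 participants would remain, not the 22 the protocol requires

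*Protocol article*

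**What the plan says.** The protocol article, Sample size calculation, makes two statements in succession.

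- From the power calculation, "the required sample size is 22 participants (11 participants per group").
- For losses, "With a 20% attrition rate, there will be a total of 26 participants for total sample (13 participants in each group").

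The inputs to the first statement are given as "With a small effect size of 0.29" and an α "level of 0.05, and power of 0.80".

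The target of 26 recurs elsewhere without change. The abstract's Methods paragraph says "This study will enroll 26 participants with mild to moderate knee osteoarthritis". Allocation sequence generation gives 13 per arm at a 1:1 ratio. Participants and recruitment presents 26 as the number that "is required to be allocated to each group", with 13 per group in brackets. That sentence repeats the target and adds no attrition figure. No section defines attrition in another way or gives a different enrolment target.

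**The concern.** An attrition rate is the share of enrolled participants who are lost. Under that meaning, the number to enrol is the required number divided by one minus the rate. The protocol's 26 is too low for this. It looks like the required number increased by 20% and then rounded down.

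On its own planning assumption, the trial would therefore be expected to finish below the size it calls required. In a trial this small, a null result will be read against the planned size, so the statement of that size should be consistent with itself. The same shortcut would also carry over to any revised base figure.

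**Working it through.** **Inputs** (protocol article, Sample size calculation)

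- Required evaluable: 22 in total, 11 per group
- Attrition: 20%
- Planned enrolment: 26 in total, 13 per group

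**1. Where 26 probably comes from.** The section shows no formula. Increasing the requirement by 20% gives 22 × 1.2 = 26.4 in total and 11 × 1.2 = 13.2 per group. Rounded down, these are 26 and 13, matching both stated figures. That the protocol was built this way is an inference. Even under this formula, rounding up gives 27 in total, or 14 per group with equal arms.

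**2. Number needed.** n/(1 − d):

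- Total: 22/0.80 = 27.5, rounded up to 28
- Per group: 11/0.80 = 13.75, rounded up to 14
- Check: 28 × 0.80 = 22.4, which meets 22

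**3. What 26 delivers.**

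- At 20% attrition: 26 × 0.80 = 20.8 in total, 13 × 0.80 = 10.4 per group
- Shortfall: 1 of 22 = 5%, or 2 of 22 = 9%
- Largest loss that still leaves 22: (26 − 22)/26 = 4/26 = 15.4%

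**4. Chance of reaching 22.** Assume each participant drops out independently with probability 0.20. The binomial probability of at least 22 completers is 38% with 26 enrolled and 68% with 28.

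**5. Effect on power.** The section does not name the test used in the power calculation or say whether α is one- or two-sided. Assume the independent t-test of the Statistical analysis section, two-sided at 0.05. With 11 per group, 80% power corresponds to a standardised difference of 1.26. Holding that difference fixed:

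| Evaluable | Power |
|---|---|
| 22 (11 + 11) | 80% |
| 21 (10 + 11) | 77.8% |
| 20 (10 + 10) | 75.7% |

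Holding power at 80% instead, the detectable difference goes from 1.26 SD at 11 per group to 1.32 SD at 10 per group.

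**6. Sensitivity to the test assumed.** The figure of 22 can also be recovered by reading 0.29 as Cohen's f in a repeated-measures group-by-time interaction, with 2 time points and an assumed correlation of 0.6. Power is then 82.5% at 22, 80.5% at 21 and 78.3% at 20. The loss is again about 2 to 4 points.

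**The case against.** The strongest reply is that the error barely matters. It moves the enrolment target by two people and costs a few points of power. The 20% is a planning guess given without a source, and 26 would still leave 22 if attrition stayed at or below 15.4%. Falling short is an expectation and not a certainty: at 20% dropout there remains a 38% chance of at least 22 completers. All of this is correct. It limits the weight of the point, but it does not make the three stated figures compatible.

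A second reply is that the base of 22 is itself doubtful, so repairing the allowance builds on weak ground. This also stands as a caution. Read as Cohen's d, 0.29 would need 188 per group for a two-sided independent t-test, and 11 per group would give about 10% power. The 1.26 and 1.32 SD figures therefore describe what 11 and 10 per group can detect. They are not the effect the protocol says it was sized on. The inflation step is nevertheless wrong whatever the base. Multiplying by 1.2 instead of dividing by 0.8 gives 1.2 × 0.8 = 0.96 of the number needed, a 4% under-enrolment before any rounding, and the absolute shortfall would grow with a larger base.

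**Conclusion.** The concern holds. A requirement of 22, attrition of 20% and enrolment of 26 are mutually inconsistent. At 20% loss, 26 leaves 20 or 21, which is 1 to 2 short, and 26 is sufficient only up to 15.4% loss. This rests on the ordinary meaning of attrition as a share of those enrolled, which nothing in the article contradicts. The cost of about 2 to 4 power points depends on an assumed test, but it is similar under both readings tried. It is a small arithmetic error in a figure the trial relies on. It should be corrected, but the correction does not establish that 22 is an adequate base.

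**What to change.** Amend the attrition sentence in Sample size calculation in one of two ways.

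- State that enrolling 26 (13 per group) allows for about 15% attrition while keeping 22 evaluable.
- Keep the 20% figure, state that about 20 to 21 participants are then expected to remain, and give the detectable difference for 10 per group (1.32 SD at 80% power, two-sided t-test at 0.05), naming the test and sidedness.

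Either costs one sentence, adds no participants and leaves the 26 quoted in the other sections unchanged. Enrolling 28 (14 per group) is needed only if the sponsor wishes to keep both the 20% allowance and the 22 evaluable. It would mean two more participants and updating the target wherever it appears.

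If the base figure is revised for other reasons, obtain the enrolment number by dividing each group's requirement by 0.80 and rounding up.

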### Statistical analysis

The collected data will be analyzed with IBM SPSS version 28.0 (IBM Corp., Armonk, NY, USA). The descriptive demographic data (means, medians, standard deviation, and frequencies) include age, gender, onset of knee OA, height, weight, knee involved, and all primary and secondary outcome measures will be computed and compared between two groups at the baseline using independent t-test. The Shapiro–Wilk test will be used to evaluate the normality assumption. A dependent *t*-test or Wilcoxon signed rank test will be performed to evaluates the difference between pre-intervention and post-intervention. The independent *t*-test or Mann–Whitney *U*-test will be performed to evaluate the difference between groups at the baseline and post-intervention. The level of significance will be set at *p* < 0.05.

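### Baseline comparison assigns a t-test to nominal variables and tests for differences that randomisation makes chance, while the post-intervention comparison leaves the baseline values unused

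*Protocol article*

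**What the plan says.** All of this stands in the Statistical analysis section of the protocol article unless another section is named.

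- The variables to be summarised "include age, gender, onset of knee OA, height, weight, knee involved, and all primary and secondary outcome measures". The summaries named are "means, medians, standard deviation, and frequencies".
- The same sentence says that these variables will be "compared between two groups at the baseline using independent t-test".
- After a Shapiro–Wilk check of normality, the section says that the independent t-test or "Mann–Whitney *U*-test will be performed to evaluate the difference between groups at the baseline and post-intervention". Baseline therefore has two named tests, chosen by normality.
- On the threshold: "The level of significance will be set at *p* < 0.05". Sidedness is not stated; two-sided is assumed below.
- No chi-square, Fisher or other test for categorical data appears anywhere in the article.
- The post-intervention comparison, as written, names no covariate and no change score.
- Allocation sequence generation: "In a ratio of 1:1, the participants will be allocated randomly", with 13 per group. No stratification is stated.
- Study design: every outcome is measured at T0 and again at T1.

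**The concern.** Two things look wrong in the baseline rule, and one follows from it.

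1. Gender and knee involved are nominal. A t-test compares means, and the mean of a set of category codes has an interpretation only when the variable has two levels. A Mann–Whitney test needs ordered values, so it is no remedy.
2. Allocation is random, so the null hypothesis of a baseline test is true by design. Any difference seen is due to chance, and the p-value neither measures how large an imbalance is nor how much it matters for an outcome.
3. The plan tests the baseline outcome values but does not then use them in the between-group comparison at T1. What is at stake is mainly precision. In a trial of 26 people, chance differences at baseline add noise to the T1 comparison, and the T0 values that could remove part of that noise are already collected.

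**Working it through.** **Inputs.** 13 per arm (Sample size calculation); 11 per arm evaluable after attrition (same section); significance level 0.05, taken as two-sided; variable list as quoted above. The article gives no figure for the baseline tests, so there is none to reproduce.

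**1. Two-level variable.** All 14 × 14 possible tables at 13 per arm were enumerated exactly.

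| True share in both arms | t-test | Uncorrected chi-square | Fisher |
|---|---|---|---|
| 50% | 0.060 | 0.076 | 0.029 |
| 30% | 0.055 | 0.056 | 0.021 |

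The t-test is close to nominal. Its decision differs from Fisher's on some tables, for example 3/13 v 8/13 and 5/13 v 10/13, where the t-test gives p < 0.05 and Fisher does not.

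**2. Three-level variable (assumption).** The article does not define the levels of knee involved. Inclusion criteria admits unilateral or bilateral disease, so left/right/both is possible. Take invented counts of left 7, right 2, both 4 in one arm and left 2, right 7, both 4 in the other.
- Coded left 1, right 2, both 3: means 23/13 = 1.77 and 28/13 = 2.15; t = −1.20 on 24 df, p = 0.24.
- Coded left 1, both 2, right 3: means 21/13 = 1.62 and 31/13 = 2.38; t = −2.55 on 24 df, p = 0.017.

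The same data are non-significant or significant according to the numbering.

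**3. Chance imbalance in a continuous variable.**
- SE of a standardised mean difference = √(2/13) = 0.392.
- P(|difference| ≥ 0.5 SD) = 2 × [1 − Φ(0.5/0.392)] = 2 × [1 − Φ(1.275)] = 0.202.
- Significance needs |t| > 2.064 on 24 df, that is, an observed difference of about 2.064 × 0.392 = 0.81 pooled SD. This happens in 5% of randomisations, almost always among those with a difference of at least 0.5 SD.
- Share of those imbalances that are non-significant ≈ 1 − 0.05/0.202 = 0.75. A simulation of 200,000 randomisations gives 0.202 and 75.4%.

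**4. Number of tests.** Six descriptors, NPRS, five KOOS subscales, four strength measures (flexion and extension, both sides) and 11 secondary measures (10-MWT at two speeds): 6 + 1 + 5 + 4 + 11 = 27. If all were independent, P(at least one p < 0.05) = 1 − 0.95^27 = 0.75. Many are related, so 75% is an upper-end value.

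**5. What the unused T0 values are worth.** Let r be the correlation between T0 and T1, which the article does not give; 0.5 to 0.7 is assumed.
- Carry-over: a 0.5 SD imbalance shifts the unadjusted T1 difference by about 0.5r, so 0.5 × 0.5 = 0.25 SD to 0.5 × 0.7 = 0.35 SD. The planned effect size is 0.29; the two are comparable only if 0.29 is a standardised mean difference, and its metric is not stated.
- Precision: ANCOVA multiplies the variance of the treatment difference by about (1 − r²)(1 + 1/(N − 4)), where the second factor is the cost of estimating the slope. With N = 22 it is 1 + 1/18 = 1.056. At r = 0.5 the product is 0.75 × 1.056 = 0.79; at r = 0.7 it is 0.51 × 1.056 = 0.54. The variance falls by about 21% to 46%. Break-even is at r² = 1/19, r ≈ 0.23; below that, adjustment costs at most about 6% in variance.

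**The case against.** The strongest case on the other side is that nothing turns on these tests.

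- *A t-test on gender is practically harmless.* This stands. Coded 0/1, it compares two proportions with type I error near 0.05. A reader might infer that the test is meaningless for gender; the figures do not support that. The dependence on coding arises only with three or more levels, and since only the most symptomatic knee enters the outcomes in bilateral disease (Inclusion criteria), a left/right coding is equally plausible.
- *The article does not use the tests to certify balance.* This also stands. A reader might infer that a non-significant result is the plan's sole evidence that the arms are comparable. The text does not say so: it attaches no decision, covariate choice or change of analysis to the baseline p-values, and comparability rests on randomisation with concealed envelopes.
- *The unadjusted T1 comparison is valid.* This stands as well. Under randomisation, chance imbalance is part of the sampling error that the test allows for, so type I error is controlled. A reader might infer that the treatment estimate is biased; it is not. Adjustment gains precision.
- *The 75% for missed imbalances follows from the 5% level and is not peculiar to this plan.* True, but it shows how little such a test says about balance in a trial of this size.

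What remains is that the named tests do not fit nominal variables, that the testing serves no purpose, and that the baseline values have a better use.

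**Conclusion.** The point holds in a limited form. As written, the plan assigns a t-test to two nominal variables and provides no suitable alternative. Its practical effect is small if both variables have two levels and arbitrary if knee involved has three, which is an assumption. The baseline tests should go because randomisation leaves them no question to answer: at 13 per arm, about 20% of randomisations show an imbalance of at least 0.5 SD in any one continuous variable, and about three quarters of those pass as non-significant. Up to 75% of trials would show at least one spurious flag among 27 tests, under independence.

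The baseline tests are a minor fault, and no trial conclusion is shown to depend on them. The main gain lies in the T1 comparison, where adjustment for T0 would cut the variance of the treatment difference by about 21% to 46% with 22 evaluable participants, if the T0–T1 correlation is 0.5 to 0.7. These figures assume roughly normal outcomes and a two-sided 0.05 level.

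**What to change.** In the Statistical analysis section:

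1. Delete the baseline significance tests, both in the sentence on descriptive data and in the later sentence that names the t-test or Mann–Whitney test at baseline.
2. State that baseline data will be described by arm: counts and percentages for gender and knee involved, means with SD or medians for continuous variables. Define the levels of knee involved.
3. Replace the unadjusted post-intervention comparison with an ANCOVA of each outcome at T1 on arm and that outcome's own T0 value, reporting the adjusted difference with its 95% confidence interval. Fix this before unblinded data are seen, for every outcome and whatever imbalance is observed.

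The cost is a change of wording. No new data, visits or participants are needed, SPSS fits the model, and fewer tests are run. If a journal insists on a baseline test, name Fisher's exact test for the nominal variables, but description alone is preferable.
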